### Follow-up

The follow-up period consists of 6 weeks. Details of pregnancy, delivery, and maternal follow-up will be recorded after 6 weeks in a case record form. If necessary, medical records of newborns will be requested (if consent is provided).

### Statistics

#### Sample size

The sample size is determined by focusing on the primary objective of the trial: the effectiveness of systematic antenatal screening on adverse small for gestational age (<10th percentile) and preterm birth (gestational age below 37 weeks). In this cluster-randomized trial, sample size depends on (1) the average risk of small for gestational age and preterm birth without the intervention (π_0_); (2) the expected effect of the intervention (π_1_); (3) the inflation factor reflecting the partial similarity/dependency of women’s outcomes or responses within the same cluster; (4) the α; and (5) power (1-β) of the test.

Based on data from the Dutch perinatal registry
[15], the average prevalence in our selected zip code areas in the years 2000 to 2008 was 16.7%. In the intervention group, we expect a prevalence of 13% at the end of the study period. The average prevalence of both primary outcomes in the Netherlands was 12% for the years 2000 to 2008
[15], and we expect a decline towards this prevalence during our study period. The inflation factor was estimated to be 2.06
[17]. This factor reflects the design effect of a cluster trial, and takes into account the degree of similarity among responses within a cluster. With five municipalities in each group (a total of ten clusters) and an alpha of 0.05 (two-sided test), 7,000 participants (3,500 per arm) should provide power in excess of 80%. This means 700 women are needed per cluster. It is assumed that a difference of 150 to 200 participants between the larger and smaller clusters has no implications for the outcome
[17].

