### Procedures, recruitment, randomization, and collection of baseline data

Randomization took place in January 2011 by an independent statistician who was not involved in executing the study. In order to decide whether matching was necessary, in each cluster, the adverse perinatal outcomes (Big 4 and perinatal mortality) were stratified according to socioeconomic status and ethnicity. Since clusters were not considerably different in terms of these characteristics, we decided that matching of clusters for socio-economic status and ethnicity was unnecessary.

As stated before, midwife practices participate in OC’s. Due to merging plans between OC’s in the north of the Netherlands, four small municipalities and one large municipality were combined and form one cluster (named Groningen). Thus, ten municipalities were randomly assigned to the intervention (n = 5) or the control group (n = 5).

In the randomization procedure, municipalities were numbered according to the expected number at risk. Hereby, we ensured that both arms of the experiment were comparable in size. Five random numbers were drawn from the uniform distribution between zero and one. If the number was below 0.5, the first of the pair would be assigned to the intervention, otherwise to the control group. The clusters Amsterdam, Tilburg, Groningen, Enschede and Nijmegen are allocated as intervention municipalities. The clusters for The Hague, Schiedam, Heerlen, Almere and Utrecht are control municipalities. The randomization scheme is available as an additional file (see Additional file
1).

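### The stated power above 80% makes no allowance for having only ten clusters; at the plan's own inputs a between-cluster test on 8 degrees of freedom has about 76%

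*Protocol article*

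**What the plan says.** All the inputs stand in the Sample size section of the protocol article. For the control arm, "the average prevalence in our selected zip code areas in the years 2000 to 2008 was 16.7" per cent. For the intervention arm, "we expect a prevalence of 13% at the end of the study period". On clustering, "The inflation factor was estimated to be 2.06", and the text explains that this factor "takes into account the degree of similarity among responses within a cluster". The design is then given as "With five municipalities in each group (a total of ten clusters) and an alpha of 0.05 (two-sided test"), and the conclusion is that "7,000 participants (3,500 per arm) should provide power in excess of 80" per cent. It adds: "This means 700 women are needed per cluster".

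The section on procedures and randomization confirms the unit of allocation: "ten municipalities were randomly assigned to the intervention (n = 5) or the control group (n = 5"). The Data analysis section plans a multilevel logistic model with random effects on the maternal and municipal levels. It names no reference distribution for the test of the intervention effect.

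**The concern.** The section lists five quantities that determine the sample size: the two risks, the inflation factor, alpha and power. The number of clusters is not among them. It enters only when 3,500 women are divided into five groups of 700.

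An inflation factor enlarges the variance of the treatment comparison. It does not reflect that this variance must be estimated from few units. The intervention differs only between municipalities, so an unmatched comparison of five with five has 10 − 2 = 8 degrees of freedom. The two-sided 5% critical value is then 2.306, not 1.96, and that gap is large enough to matter when power is claimed to be just above a threshold.

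This is the article's only power statement for its main effectiveness objective. If the trial finds no effect, readers will credit it with a better chance of detecting the planned difference than a test at a true 5% level provides.

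**Working it through.** **Inputs** (all from the Sample size section): control prevalence 0.167; intervention prevalence 0.13; 3,500 women per arm; five clusters of 700 per arm; inflation factor 2.06; two-sided alpha 0.05. Equal cluster sizes and no losses are assumed.

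**Step 1: standard error of the difference.**
- Binomial variances: 0.167 × 0.833 = 0.1391 and 0.13 × 0.87 = 0.1131; sum 0.2522.
- SE = √(0.2522 × 2.06 / 3,500) = 0.01218.
- Standardised difference = 0.037 / 0.01218 = 3.04.

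**Step 2: reproduce the plan's figure.** With a normal critical value, power = Φ(3.04 − 1.96) ≈ 85.9%. This agrees with the stated claim. By the same route, 80% power needs 1,449 women per arm before inflation, and 1,449 × 2.06 ≈ 2,985 after it, which is below the planned 3,500.

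**Step 3: same inputs with 8 degrees of freedom.** Critical value 2.306; noncentral t with noncentrality 3.04.

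| Calculation on 8 df | Power |
|---|---|
| Unpooled variance | 75.8% |
| Pooled variance | 75.7% |
| Log-odds scale | 75.5% |
| Simulation: 200,000 trials, 5 + 5 clusters of 700, beta-binomial, cluster-level t-test | 75.9% |

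The simulation used the intracluster correlation implied by the plan: (2.06 − 1) / (700 − 1) ≈ 0.0015.

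**Step 4: what 1.96 would do to alpha.** The two-sided tail of a t distribution on 8 df beyond 1.96 is 8.6%. In simulation with no effect, a cluster-level test rejected 8.5% of the time with 1.96 and 5.0% with 2.306.

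**Step 5: what 80% would take on 8 df.**
- Same size and inflation factor: an intervention prevalence of about 12.8%, a difference of 3.9 points instead of 3.7.
- Same prevalences and size: an inflation factor of at most about 1.85.

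**Step 6: dependence on the test.** A mixed model does not let the between-cluster variance go below zero, which uses some knowledge of the binomial variance. In a normal-theory simulation with equal clusters, with the critical value calibrated to exactly 5% at the assumed intracluster correlation, power was about 79% with a REML variance and about 80% with an ML variance.

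**The case against.** The strongest reply is that 76% belongs to one particular test, an unweighted cluster-level t-test, whereas the plan uses a multilevel logistic model whose reference distribution may properly be settled in an analysis plan that is not shown. Part of this stands. As step 6 shows, a bounded variance with a suitably calibrated critical value recovers most of the loss. That calibration holds only near the assumed intracluster correlation, however, and even then it reaches roughly 80% and does not exceed it with any margin. Nor is the point about a missing analysis detail: the article gives a power figure together with its inputs, and those inputs do not support it.

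A second reply is that the gap lies within the uncertainty of the inputs. This is fair. On 8 df, power is about 81% at an inflation factor of 1.8. If the intervention prevalence fell to 12%, the national figure that the article quotes, power would be about 93%. But the claim is made for 13% and 2.06.

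A reader might also infer more than the documents support:

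- *That clustering was overlooked.* It was not. The same section names the ten clusters and applies a design effect; only the allowance for degrees of freedom is absent.
- *That the authors used normal quantiles.* This is likely, since that route reproduces a figure above 80%, but the cited formula is not shown. It remains an inference.
- *That the claimed power requires a test with a true alpha near 10%.* A cut-off of 1.96 in a cluster-level test gives about 8.6%, and reaching just 80% power on 8 df takes an alpha of only about 6.4%.
- *That only 4 df are available, because allocation was made within pairs ordered by size.* No paired analysis is planned. The randomization section judges matching on socioeconomic status and ethnicity unnecessary and uses the size ordering to balance the arms in size.

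**Conclusion.** The point holds as a modest overstatement of power. At the plan's own inputs, a between-cluster test on 8 df at a true 5% level has about 76% power, against a stated figure above 80% and a normal-approximation figure of 85.9%. That is about a one-in-four chance of missing the planned effect.

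The result rests on an unmatched comparison with no cluster-level covariates, equal clusters of 700, complete outcomes, and 16.7% versus 13% as the single tested endpoint, as the Sample size section treats it. Unequal cluster sizes would lower power somewhat further.

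It should be corrected, but it is not a fatal flaw. The shortfall is a few percentage points, it varies with the test adopted, and it does not show that the design or the planned model is invalid.

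**What to change.** In the Sample size section, replace the claim with one of two statements: power of about 76% for 16.7% versus 13% under a between-cluster test on 8 degrees of freedom with an inflation factor of 2.06; or a difference of about 16.7% to 12.8% detectable with 80% power under the same conditions. Quoting the implied intracluster correlation (about 0.0015 at 700 women per cluster) would help readers but is optional.

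The cost is one reworded sentence and a slightly less favourable figure. The numbers of participants and clusters stay as they are.

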#### Data analysis

Data will be analyzed according to the intention-to-treat principle. The effectiveness of the R4U scorecard, corresponding care pathways and multidisciplinary consultation versus conventional antenatal healthcare (measured as the difference in small for gestational age and preterm birth between both groups) will be assessed by using multilevel logistic regression with random effects. Results will be presented as effect estimates with a measure of precision (95% confidence interval). Data will be analyzed anonymously on two levels: the maternal and the municipal level. To guarantee anonymity, we will not analyze the data on community practice or at the hospital level. Study participants, municipalities, and community practices or hospitals will not be traceable. Other analyses related to our intervention are based on differences in other birth outcomes (for example, Apgar score), the number of referrals between community midwives and gynecologists, adequacy in risk assessment (for example, detection of growth restriction in the antenatal phase), and the contribution of nonmedical risk factors to adverse birth outcomes between the intervention and control group. These outcomes will be assessed with univariate and multivariate regression analysis with 95% confidence intervals.

### Ethical considerations

This study has been approved by the Ethics Committee of the Erasmus Medical Center Rotterdam (Ref. No. MEC-2012-322) and by the management of participating hospitals that requested an extra review (see Additional file
2).

All participants will receive written and oral information about the study, after which informed consent will be obtained. Participation is voluntary and no extra incentives will be provided.

## Discussion

The main objective of this trial is to investigate the effectiveness of a new systematic approach in antenatal healthcare on adverse pregnancy outcomes and efficacy of implementation. We will implement and investigate the Rotterdam Reproductive Risk Reduction (R4U) scorecard and corresponding care pathways in 14 municipalities.

The study meets the current evidence to intervene early in pregnancy upon (modifiable) risk factors associated with adverse perinatal health outcomes. We aim to target a population that potentially will benefit the most with the use of selected geographical areas. With the use of care pathways, optimal linkage is sought between curative and preventive care, such as public health, government, and social welfare organizations
[14].

To our knowledge, this is the first approach in antenatal healthcare whereby systematic risk selection for both medical and nonmedical risk factors, variable thresholds, tailor-made care pathways, and structured consultation between midwives, gynecologists and other care providers are combined. This study will introduce a systematic approach in antenatal health care, which may improve perinatal outcomes and, thereby, future health status of a new generation in the Netherlands.

### Trial status

Recruitment started in August 2012, and the first included study participant delivered in March 2013. The trial is currently recruiting study participants.

## Abbreviations

HP4ALL: Healthy Pregnancy 4 ALL
OC: obstetric collaboration
PRN: Perinatal Registry Netherlands
R4U: Rotterdam Reproductive Risk Reduction.
